### Skill set needed

At least 5 years’ experience of facilitating creative Art for Health groupsAbility to hold a safe space where individuals can express themselves in confidenceFamiliarity with mixed-media and arts in generalWillingness to follow/support participants’ emerging interestsCommitment to documenting/reflecting on sessions personally/within research group.A researcher will be ‘on hand’ at the venue in case any additional help is needed (eg, participant unwell), but will not be directly involved in the session. The level of support provided will be assessed to determine the need for a second person being available in a future trial.

### Usual Care

In Bournemouth, support is provided by the Early Supported Discharge multidisciplinary team for 2–6 weeks after leaving hospital and then medical care via the GP, with a referral to the Stroke Coordinator. People with complex medical conditions are seen by Stroke Consultants as hospital outpatients. Ongoing rehabilitation needs are met by rehabilitation teams and in some areas day hospital service provision.

In Cambridgeshire, medical care is delivered via the GP and people with complex medical conditions are seen by Stroke Consultants as hospital outpatients. All can access support from the Stroke Association ‘Information, Advice and Support Coordinator’ and may receive additional therapy or support via one of three locality neurorehabilitation teams. Participants in both arms of the trial will receive usual care, and usual care will not be affected by involvement in the trial.

### Outcome measures and blinding

As one of the objectives of this feasibility study is to refine the selection of outcome measures for a subsequent full trial we have included a broad range of outcomes and are exploring the extent to which participants require support to complete them.

In the HoS arm, outcome measures will be administered within 1 month prior to the HoS group (baseline) and then approximately 1 month following its conclusion. For those allocated to the usual care arm, outcomes will be administered within an equivalent time frame. Outcome measures are all self-reported and presented in a booklet in a large font.

At baseline, outcome measures will be administered face-to-face by a research assistant in participants’ homes. At approximately 5 months postrandomisation (1 month post-HoS intervention) outcomes will be administered by post, or if needed, with face-to-face or telephone support from a blinded assessor. Support needs will be logged. Participants will be asked not to disclose their allocation arm to the blinded assessor. The assessor will log allocation beliefs and instances of unblinding.

#### Demographic/descriptor variables

Age, gender, marital status, educational qualifications, ethnicity, household composition, employment situation, comorbidities and medication will be recorded at baseline.

#### Stroke-related information

Type, side-of-stroke and time-since-stroke, mobility (Rivermead Motor Assessment—Gross Motor subscale^61^), upper limb impairment (Motricity Index^65^), communication ability,^66^ cognitive ability.^67^

##### Proposed Possible Primary Outcomes for a future trial

Mental Well-being—Warwick and Edinburgh Mental Well-Being Scale (WEMWBS)^68^Anxiety and Depression—Hospital Anxiety and Depression Scale (HADS)^69^Quality of Life—ICEpop CAPability measure for Adults (ICECAP-A)^70^

##### Proposed Possible Secondary Outcomes for a future trial

Self-esteem—Rosenberg Self-Esteem Scale (RSES)^71^Self-concept—Self-concept Head Injury Semantic Differential Scale (HISDIS)^72^Quality of Life—Medical Outcomes Short Form-36 (SF-36) (V.1)^73^

##### Process measures

Views of recruitersNumber of people approached, number eligible, number who agree to be contacted/to take partShort-term study retention rates (until 1-month postgroup time point)Group attendance rates/group sizes and composition, reasons for non-attendance (where known)Number of questionnaire reminders sent/participants requiring support to complete outcomes and levels/patterns of missing dataSense of belonging in the group at first, fifth and last HoS session (Doojse scale^74^)Number of participants in the HoS group who contact group members outside the group settingPostsession reflection notes kept by the HoS artist facilitators.

### Participant withdrawal from the intervention and/or research follow-up

Participants will be informed that they can withdraw from the study at any time without their care being affected in any way. If a participant withdraws consent to be included in research follow-up during the feasibility trial, the study research assistant at the centre will be informed and will contact the participant. If a participant in the HoS arm wishes to withdraw from the intervention, the research assistant will determine whether he/she also wishes to withdraw from the research follow-up. For those wishing to withdraw from the research follow-up, the research assistant will determine whether the participant is willing for data collected before withdrawal to be used at final analysis, or whether this information should be destroyed. No data will be used in the final analysis without a participant's consent.

### Data protection and data storage and management

All data will be handled, stored and protected in accordance with the Data Protection Act (1998) and the NHS Code of Confidentiality (2003). Data will be anonymised and only accessible to authorised staff working on the study.

Data processing, management, validation and quantitative analysis activities will be overseen by the Bournemouth University Clinical Research Unit and conducted in accordance with their standard operating procedures to ensure a clear audit trail and that relevant regulatory governance requirements are met.

The primary source of quantitative data will be questionnaire-based participant reported measures, but additional data will include recruitment logs kept by the Clinical Research Network funded researchers and by the study research assistants and attendance logs kept by the HoS artist facilitators. Data will be anonymised and single entered onto a password protected SPSS (V. 21) database stored on a secure backed-up university networked drive by the research assistant at the lead centre. A random sample of 20% of the data will be rekeyed (by ST) to check data quality. The resultant data will be cross-checked and differences resolved by referring back to the primary source. Any changes to data points will be documented to ensure a clear audit trail. Prior to the main analysis, statistical data checks will be carried out (eg, range checks). The database will then be closed to further changes.

Digital audio recordings of interviews and transcripts (see later) will be stored in secure password protected files on a backed-up university networked drive.

### Statistical analysis

This is a feasibility study and so the aim is not to provide a fully powered hypothesis test of the effectiveness of the intervention.^75^ Instead, analyses will focus on estimating key feasibility study parameters. We will also develop and test out data analysis procedures, with the particular aim of informing the statistical analysis plan for a full trial. Preliminary estimates of effect size (with 95% CIs) for potential primary outcome measures will be calculated so that these can inform the plausibility of the effect sizes used in future sample size calculations.

The main statistical analysis will be carried out using IBM SPSS software and will also include:
Producing a CONSORT diagram to represent numbers of stroke survivors eligible for inclusion, recruited, randomised and completed;Descriptive statistics (with 95% CIs) will be used to summarise data relevant to recruitment, attrition, outcome measures, process measures, return rates and attendance at HoS sessions;SDs (95% CI) of potential primary outcome measures will be estimated;Rates and patterns of missing questionnaire data will be examined to inform a strategy for dealing with missing data in a full trial;NHS and social care use will be summarised via descriptive statistics, and we will derive QALY estimates from SF-6D utility scores.

### Feasibility economic evaluation component

The future study will include a full within-trial economic evaluation, comparing the cost of delivering treatment in both arms in relation to quality adjusted life years (QALYs) in the primary analysis, and the primary clinical outcome of choice in secondary analysis. The primary analyses will take on the health and social care payer perspective, with secondary analysis from a societal perspective on costs.

In this feasibility economic evaluation, the data collection tools to collect resource use and costs for the future trial will be developed and refined. We will develop case report forms for the artist facilitators to complete with resources required to deliver the HoS intervention: preparation time, contact time and travel time, materials used, venue, numbers of participants attending the session and supervision required. Resources required to deliver care in both arms will be collected from a telephone-administered resource use questionnaire, administered to the participant or their carer, at 5 months postrandomisation, and a prospectively completed resource use log to use as a memory aid.^76^ Examples of resources that will be included are GP visits, informal care, productivity losses, use of social services and medications.

We will report a preliminary estimate of the cost of delivering the HoS intervention using a microcosting approach. We will use UK preference-based tariffs to the SF-6D and ICECAP-A generic scores to derive short-term quality adjusted life years (QALYs) estimates at follow-up per arm. Levels of missing data per cost category will also be reported. We will develop strategies to address missing data in poorly completed resource use categories for the future trial. Our experiences of data collection in the feasibility study will be useful in enabling refinement of the tools and methods to be used in the full-scale trial.

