### Study design

This is a 24-month two-centre parallel arm pragmatic randomised controlled feasibility study of a HoS group plus usual care compared with usual care alone (see figure 1), with nested economic and qualitative components. We are using a usual care comparator in order that the future trial will reflect real-world effectiveness of this complex intervention. A nested qualitative interview study will provide insights into individuals’ experiences of participating and the acceptability of study processes, the HoS intervention and outcome measures. The feasibility economic component will enable us to pilot methods to collect intervention costs and resource utilisation to inform the future trial design and within-trial economic evaluation. These trial processes will be tested for a follow-up period of 5 months postrandomisation. The definitive trial would include longer follow-up to capture the longer term health and economic benefits of treatment delivery.

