### Sample size considerations

A sample size of 64 will be adequate to estimate, to an acceptable degree of precision, the key parameters needed to address the study objectives. A questionnaire return rate of 80% would mean data at baseline and 1 month postintervention would be available for 51 participants. Estimating the recruitment rate will help us to plan the full-scale RCT. Precision of this estimate will be summarised using the distance from the estimate to the upper/lower limit of the 95% CI. With a total sample size of 64, the recruitment rate will be estimated with a precision of ±6% (assuming a recruitment rate of 30%). Assuming a questionnaire return rate of 80%, the return rate (in the short term) will be estimated with a precision of ±10%. We aim to estimate the SD of potential primary outcome measures in preparation for a formal sample size calculation for a larger RCT. Assuming these outcomes are standardised (SD of 1), the precision (as summarised by SE) will be 0.1 based on n=51 with follow-up data. For the full trial, the sample size calculation will be inflated appropriately to take into account potential clustering effects due to the group-based nature of the intervention.^60^ The aim is not to test the effectiveness of the intervention. However, we will take into account the magnitude of the estimated effect size (95% CI) when considering the plausibility of effect sizes to be used in the sample size calculation for the full trial.

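### The economic section derives QALYs from ICECAP-A as well as SF-6D; the statistical section names SF-6D alone, and a capability index does not yield QALYs

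*Protocol article*

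**What the plan says.** Two sections of the protocol article describe how QALYs will be obtained.

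- *Feasibility economic evaluation component*: "We will use UK preference-based tariffs to the SF-6D and ICECAP-A generic scores to derive short-term quality adjusted life years (QALYs) estimates", at follow-up and per arm. Both instruments are named, and QALYs are the only stated product.
- *Statistical analysis*, last item of the list: "we will derive QALY estimates from SF-6D utility scores". ICECAP-A does not appear in this item.

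The outcome lists show what the two instruments are. ICECAP-A is a possible primary outcome for the future trial, under quality of life, with its name given in full as "ICEpop CAPability measure for Adults (ICECAP-A"). The possible secondary outcomes include "Medical Outcomes Short Form-36 (SF-36) (V.1"), the instrument from which SF-6D is ordinarily scored.

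The economic section also sets the role of QALYs in the future trial, where costs will be compared "in relation to quality adjusted life years (QALYs) in the primary analysis, and the primary clinical outcome of choice in secondary analysis".

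**The concern.** A QALY weights time by a health utility on a scale where dead is 0 and full health is 1. A capability index weights time by something else. If the economic section is followed literally, the report could give two figures per arm, both labelled QALYs, on scales with different meanings. The article gives no rule for choosing between them.

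What is at stake is what the feasibility study hands on. Its economic component exists to pilot methods for a future evaluation whose primary analysis is in QALYs. The future trial is also meant to keep that primary analysis apart from a secondary one on the chosen clinical outcome, for which ICECAP-A is a candidate. If ICECAP-A were chosen and also treated as a QALY source, one instrument would feed both analyses and the distinction would blur.

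**Working it through.** **No figure to reproduce.** The article gives no utility, tariff value or QALY estimate, so the check is mainly a comparison of text.

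**1. Source of QALYs, side by side.**

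| Section | Instruments named | Stated product |
|---|---|---|
| Feasibility economic evaluation component | SF-6D and ICECAP-A | QALYs |
| Statistical analysis | SF-6D | QALYs |

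The sections differ on whether ICECAP-A contributes.

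**2. Does anything else in the article rescue the literal reading?** Three things could: a mapping from ICECAP-A to health utility, a separately named capability outcome such as years of full capability, or a rule saying which QALY estimate takes precedence. None appears. The statistical section uses the word utility for SF-6D alone.

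**3. What an ICECAP-A tariff times time would measure.** The article supplies the instrument's name, which identifies it as a capability measure. The anchoring of its tariff (none to full capability) is general methodology brought in here. On that basis the product of index and time is in capability-years.

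**4. Scale, for illustration only.** The article states: "These trial processes will be tested for a follow-up period of 5 months postrandomisation". With an index held constant over T years, the accrued quantity is index × T.

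- T = 5/12 = 0.417 years, which is also the most that can accrue at an index of 1.
- Let d be the gap between the ICECAP-A and SF-6D index values for the same person. The documents give no value, so assume d = 0.1 to 0.2.
- The shift in the 5-month figure is d × T: 0.1 × 0.417 = 0.042, and 0.2 × 0.417 = 0.083.
- Example with assumed values of 0.6 (SF-6D) and 0.8 (ICECAP-A): 0.6 × 5/12 = 0.250 and 0.8 × 5/12 = 0.333, a difference of 0.083.

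This is an offset in level. If the same offset d applies in both arms, the between-arm difference on ICECAP-A is [(s₁ + d) − (s₀ + d)] × T = (s₁ − s₀) × T, where s₁ and s₀ are the arms' mean SF-6D values, and d cancels. The illustration therefore says nothing about the size of a treatment effect on either scale.

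**5. Does any planned figure depend on this?** The precision figures under *Sample size considerations* reproduce without any utility value:

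- Recruitment rate: 64/0.30 = 213 approached; 1.96 × √(0.3 × 0.7/213) = 6.1% (stated 6%).
- Return rate: 1.96 × √(0.8 × 0.2/64) = 9.8% (stated 10%).
- SE of a standardised SD with n = 51: 1/√(2 × 50) = 0.100 (stated 0.1).

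None would change.

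**The case against.** The best defence is condensed drafting. A journal article may have packed two instruments and two tariffs into one sentence, meaning QALYs from SF-6D plus a separate ICECAP-A index. The use of utility for SF-6D alone fits that, and the full protocol is not shown. This is plausible, but it is not what the sentence says, and a reader following it would compute QALYs from both.

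A second defence is that the statistical section offers one item in a list, while the economic section is the fuller account. This partly stands. A reader might infer a flat contradiction, with the statistical section confining QALYs to SF-6D. It contains no such restriction: it names SF-6D and is silent on ICECAP-A. The sections are inconsistent, but neither denies the other.

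Third, the tariff anchoring is not in the documents. That is correct, and the point is labelled accordingly. The inconsistency between the sections stands without it.

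Fourth, the consequences are limited. The article says of this study: "The aim is not to test the effectiveness of the intervention". The QALYs are a short-term descriptive output, and both instruments are collected in any case, so a mislabelled figure could be corrected at reporting with no data lost. This stands and lowers the severity.

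**Conclusion.** The point holds as an inconsistency on the QALY source, together with a stated derivation that, followed literally, would label capability-years as QALYs. The second part rests on the standard understanding of the ICECAP-A tariff, which the article supports only by naming the instrument a capability measure. Severity is minor to moderate. The effect is confined to descriptive economic outputs and what they pass to the future cost-per-QALY analysis; recruitment, retention, attendance and sample-size precision are unaffected.

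Two stronger inferences are tempting and not supported:

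- That the gap between the two indices is large compared with a plausible treatment effect. The index values are assumed, the documents give no treatment effect on either scale, and an offset in level is not a between-arm contrast.
- That invalid QALY standard deviations would enter the future sample size calculation. The planned SDs are those of the potential primary outcomes (WEMWBS, HADS and ICECAP-A scores); no QALY SD is planned.

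Nor is the absence of detail on how QALYs are accumulated over time or adjusted for baseline part of this point. Such detail is commonly left to an analysis plan.

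**What to change.** In the feasibility economic section, state that QALYs will be derived from SF-6D only. Add that ICECAP-A tariff values will be reported separately per arm as a capability outcome and will not be called QALYs. Align the statistical analysis item by keeping SF-6D as the QALY source and mentioning the separate ICECAP-A summary.

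The cost is wording only. SF-36 and ICECAP-A are already among the measures administered at baseline and at about 5 months, so no new data, participant burden or change in sample size is involved.

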### Qualitative component

To gain valuable in-depth data about study processes and the HoS intervention,^77^ 12 (8 intervention; 4 control) face-to-face interviews (in participants’ homes) will be conducted across both centres by [name] at (1) postrandomisation but preintervention, and (2) after all the assessments are completed at 5 months postrandomisation (24 interviews in total). Purposive sampling will be used to capture variations that may influence perceptions, including age, gender, communication disability and severity of stroke.

Interviews will include: (1) *research aspects—*reasons for participation, acceptability of trial processes/outcome measures/feedback for improvement of participant experience/perceived willingness to complete longer term follow-ups (2) *intervention aspects* (intervention arm only)—expectations and experience of the intervention, acceptability of venue/intervention, ability/willingness to pay for own transport costs. (3) *stroke aspects* (both)—experience of well-being/self-confidence.

The artist facilitators will keep weekly postsession reflections. With participants’ permission, work created will be photographed by the artist facilitators to explore changes over time.

Interviews will be transcribed verbatim. Each transcript will be read and re-read in detail and codes related to the three aspects covered in the interview will be noted, namely; (1) research (2) intervention (3) stroke confidence/well-being. Each transcript will be read and coded independently by [name], FR and KG. Following this, similarities and differences across transcripts will be noted and initial understandings will be made for each iteration. For simple aspects (such as the cost of transport), the analysis will be at the level of content analysis.^78^ For more complex aspects (such as participants’ expectations/experiences) themes will be produced and a thematic analysis carried out.^79^ During this process, the researchers will meet to discuss their codes, similarities and differences in order to highlight alternative interpretations which may have been missed. Finally, the similarities and differences across all four iterations will be discussed in relation to the aspects listed in (1), (2) and (3) as described above.

Each artist facilitator's weekly reflections will be discussed with the CI ([name]) and PI (FG), and key points shared with the research team to inform training and standardisation of the approach for the full trial.

### Project management and safety monitoring

The chief investigator (CI) will have overall responsibility for study conduct and will liaise closely with the Bournemouth University Clinical Research Unit. At the lead centre, [name] (CI), PT (study statistician) and ST (methodologist) will have regular meetings to discuss study progress. The research assistants at each centre will deal with the day-to-day management and coordination of the study, and will have regular meetings with the PI at each centre and will call on other research team members as appropriate. The CI, PI and research assistants will have Skype meetings every 2–3 weeks. A project management group comprising all coapplicants, study staff and PPI representatives will meet five times over the course of the study with service user group meetings held on three of those 5 occasions. The study steering group (independent representative, CI, PI, statistician, PPI representative and representatives of the sponsor) will meet bi-annually to monitor progress.

Adverse events (AEs) will be closely monitored and reported to a Core Safety Team ([name], FG, PT and ST). During all telephone and face-to-face contact meetings, the study research assistants will ask participants if they have experienced any AEs and log these. The HoS artist facilitators will be asked to record any AEs and report these to the local study research assistant. The Core Safety team will consider the events and offer advice to the project team. The CI will assess an AE to establish if it is a serious adverse event (SAE) according to the National Research Ethics Service (NRES) definition. If the AE is not defined as serious it will be recorded on a case report form and stored in the site file, and the participant will be followed up by the research team as deemed appropriate and where required. Reports of related and unexpected SAEs will be submitted to the NHS Research Ethics Committee (REC) within 15 days of the CI becoming aware of the event using the ‘Report of SAE form for non-CTIMPs’ (V.3 April 2007), published on the NRES website. The sponsor will be notified within 24 h.

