### HeART of Stroke Group Intervention

Sessions will be held in community venues recommended by service users that have good accessibility, parking and public liability insurance.

Ten 2 h HoS group sessions will be held in a community venue over 14 weeks (table 1). Based on service user suggestions made when we were designing the intervention, session frequency will be tapered to support the postgroup transition (first 7 sessions held weekly, sessions 8–9 fortnightly and session 10 held 3 weeks later). It will be a closed group of 6–8 participants with a focus on the person rather than his/her stroke.

**Table 1 BMJOPEN2015008888TB1:** HeART of stroke group intervention

Session number	Focus of session
1–3	Introductions and initial exploration
4–7	Group members encouraged to co-facilitate/engage in self-directed creative practice within sessions and at home
8–10	Ongoing sessions as well as opportunities for group community visits

The essential features of the group are the opportunity to be creative and the safe group atmosphere created and maintained by the artist facilitator. Within neuropsychological rehabilitation, it is hypothesised that establishing a safe place where clients feel understood and supported can facilitate self-development.^30^
^62^ Creative activities allow access to internal resources and non-verbal/emotional as well as rational ways of knowing and build skills to foster self-esteem.^34^
^63^ Members will be encouraged to (1) explore their sense of self and support others’ explorations; (2) be non-judgemental of self/others; (3) exercise personal choice; (4) develop a sense of play/improvisation.

Each week the artist facilitator will prepare resources in response to the group's creative interests and skills, including paints, drawing materials, clay, textiles and mixed-media. The group will be offered ‘stimulus’ pieces, such as books, poems, images, music and films, and be encouraged to bring pieces of interest to the group. They will be supported to explore their new lives through reflection, using imagination and engagement in arts-practice.^64^ Following each session, the artist facilitator will briefly document observations and reflect further to inform the selection of major provocation/stimulus materials for the next session.

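### Adverse events have a reporting route in the HoS arm that usual care lacks, so recorded counts by arm are not comparable as the procedure is described

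*Protocol article*

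**What the plan says.** Project management and safety monitoring sets two routes for AEs. The first is nominally common to both arms: "During all telephone and face-to-face contact meetings, the study research assistants will ask participants if they have experienced any AEs and log these". The second runs through the people who deliver the intervention: "The HoS artist facilitators will be asked to record any AEs and report these to the local study research assistant".

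The contacts that feed these routes are described elsewhere in the article:

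- HoS arm: "Ten 2 h HoS group sessions will be held in a community venue over 14 weeks" (HeART of Stroke Group Intervention), spaced as "first 7 sessions held weekly, sessions 8–9 fortnightly and session 10 held 3 weeks later". Under Skill set needed, a researcher is also "at the venue in case any additional help is needed", though not taking part in the session.
- Both arms at about 5 months: "outcomes will be administered by post, or if needed, with face-to-face or telephone support from a blinded assessor" (Outcome measures and blinding). Post is therefore the default.
- Both arms at 5 months: "a telephone-administered resource use questionnaire, administered to the participant or their carer, at 5 months postrandomisation" (Feasibility economic evaluation component). A resource-use log kept during follow-up serves as the memory aid. The article does not say who makes this call.
- Interviews: 8 HoS and 4 control participants, each seen before the intervention and after the 5-month assessments (Qualitative component).

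The summaries listed under Statistical analysis do not name AEs, and no comparison of AEs between arms is stated.

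**The concern.** A count of AEs by arm can be read as a comparison only if both arms are asked in the same way and about equally often. Here one route can exist in the HoS arm only. The yield of the other depends on how often a research assistant speaks to the participant, and usual care has very few such contacts described. An event in usual care, such as a fall or an admission, may come to light only at 5 months, or not at all. The same event in a HoS participant could be noticed at the next session.

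The expected direction is more recorded events on HoS with no difference in true risk. At stake is the reading of any AE counts shown by arm, and the procedure itself. The study exists to settle methods for a definitive trial, and an unequal AE procedure carried into that trial would bias its safety comparison by an amount that a larger sample does not reduce.

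**Working it through.** The article gives no AE rate, capture rate or AE table, so there is no stated AE figure to reproduce. The check is a count of described contacts, followed by an illustration on assumed values.

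**1. Session schedule.** Seven weekly sessions fall in weeks 1 to 7, two fortnightly sessions in weeks 9 and 11, and the last three weeks later in week 14. That is 7 + 2 + 1 = 10 sessions ending in week 14, which agrees with the article's ten sessions over 14 weeks.

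**2. Scheduled occasions after randomisation on which an AE could be captured, for every participant in the arm.**

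| Source | HoS | Usual care |
|---|---|---|
| Group sessions (facilitator route) | up to 10 | 0 |
| Outcome booklet (post by default) | 0 | 0 |
| 5-month resource-use call | 1 | 1 |
| Total | up to 11 | 1 |

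These are opportunities, not confirmed enquiries. The HoS figure assumes full attendance. The consent and baseline visit precedes randomisation and does not count.

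**3. Contacts for some participants only.** With 64 randomised 1:1, there are about 32 per arm. Interviews reach 8/32 = 25% of HoS and 4/32 = 12.5% of usual care, so they do not redress the balance. Support with the outcome booklet is given only where needed.

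**4. Strength of the one common contact.** Research assistants must ask about AEs at telephone contacts, but the caller for the resource-use questionnaire is not named, so it is unclear whether that duty applies. A carer may answer in place of the participant. The memory aid records resource use, not AEs.

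**5. Illustration.** Suppose the true proportion with an AE is p in both arms, and capture probabilities are d_H (HoS) and d_U (usual care). The expected number of participants with a recorded AE is 32 × p × d, and the apparent ratio is d_H/d_U. All of p, d_H and d_U are assumptions. With p = 0.40 and d_H = 0.9, HoS gives 32 × 0.40 × 0.9 = 11.5.

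| d_U | Usual care, 32 × 0.40 × d_U | Apparent ratio, 0.9/d_U | Apparent difference, 0.40 × (0.9 − d_U) |
|---|---|---|---|
| 0.9 | 11.5 | 1.0 | 0 |
| 0.7 | 9.0 | 1.29 | 0.08 |
| 0.5 | 6.4 | 1.8 | 0.16 |
| 0.3 | 3.8 | 3.0 | 0.24 |

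**6. Against sampling error.** Take d_U = 0.5, so the recorded proportions are 0.36 and 0.20. The 95% half-width for their difference is 1.96 × √(0.36 × 0.64/32 + 0.20 × 0.80/32) = 0.216, which exceeds the spurious difference of 0.16. In this study, chance alone could produce a gap of that size. In a larger trial the half-width shrinks and the spurious difference does not.

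**The case against.** The strongest reply is that no stated analysis is harmed. AEs are handled case by case: the Core Safety Team considers them, the chief investigator judges seriousness, and related and unexpected serious events go to the ethics committee. For that purpose an extra route at the point of delivery is protective, since distress or illness during a session can arise only in HoS. The article expects few risks from the intervention. It is also a condensed account, and the full protocol may describe further contacts. This stands, and it limits the consequence to how counts by arm are read and to what the full trial inherits.

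A reader might infer three stronger things that the article does not support.

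- *That AEs are recorded at every HoS session.* Facilitators are asked to record any AEs. No frequency or active questioning is stated, and the researcher at the venue is there in case help is needed.
- *That the arms will differ.* The resource-use log, whose examples include GP visits and medications, may help participants recall events that led to care. If a research assistant makes the 5-month call, AEs should already be asked about then. Good recall could close much of the gap.
- *That the ratio is about 1.3 or 1.8.* Those values only restate the assumed capture rates and are not evidence of size.

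None of this removes the asymmetry. One route is confined to HoS by its nature, and the article describes no equivalent for usual care.

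**Conclusion.** The point holds as a matter of expected direction. As described, the procedure gives HoS an AE route that usual care lacks, and the shared route has one described contact for all usual-care participants after randomisation. Recorded AE counts are expected to be higher in HoS even when the true risk is equal. The size cannot be derived from the article; under the assumed capture rates the apparent ratio lies between 1.0 and 3.0.

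The conclusion rests on two assumptions: that the article describes the routine contacts completely, and that more occasions for reporting lead to more events being recorded. The feasibility objectives are not threatened, and no planned test is invalidated. The change is worth making because it is cheap and because the definitive trial is likely to take over the procedure tried here.

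**What to change.** State that the 5-month call in both arms includes one fixed set of AE and serious AE questions covering the whole period since randomisation, and name who makes the call. To protect blinding, ask these questions after the outcome measures are complete, or have someone other than the blinded assessor ask them. Base any by-arm AE summary on this common source alone, giving the number of participants reached in each arm. List facilitator-reported events separately as safety data from the HoS arm only. All existing HoS safety reporting stays in place.

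The cost is a slightly longer call and one extra table. The by-arm summary would then rely on recall over about 5 months and on participants who can be reached, so it will probably miss minor events. It should miss them to a similar degree in both arms, which is what a comparison needs.
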